### Eligibilty criteria

Inclusion criteria:Diagnosis of isolated dystonia (focal, segmental or generalized) treated by bilateral deep brain stimulation of the internal globus pallidusSufficient time to complete clinical DBS programming after DBS surgery (> 6 months)Deep brain stimulation settings and dystonia medication stable for at least 3 monthsUnderstanding and agreement to the study and signed informed consentExclusion criteria:Relevant comorbidities that might interfere with study endpoints (esp. palliative disease and severe neurologic or psychiatric comorbidities).

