## Abstract

**Introduction:**

Deep brain stimulation of the internal globus pallidus is an effective treatment for dystonia. However, there is a large variability in clinical outcome with up to 25% non-responders even in highly selected primary dystonia patients. In a large cohort of patients we recently demonstrated that the variable clinical outcomes of pallidal DBS for dystonia may result to a large degree by the exact location and stimulation volume within the pallidal region. Here we test a novel approach of programing based on these insights: we first defined probabilistic maps of anti-dystonic effects by aggregating individual electrode locations and volumes of tissue activated of > 80 patients collected in a multicentre effort. We subsequently modified the algorithms to be able to test all possible stimulation settings of de novo patients in silico based on the expected clinical outcome and thus potentially predict the best possible stimulation parameters for the individual patients.

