## Introduction

Dystonia is a central nervous system disease associated with sustained or intermittent muscle contractions causing abnormal, often repetitive, movements, postures, or both [1]. Activities of daily living, social participation and quality of life can be markedly impaired in dystonia due to pain, reduced overall mobility and stigmatization [2, 3].

Deep brain stimulation (DBS) is a surgical therapy for a variety of neurological and psychiatric disorders that uses continuous electrical stimulation of deep brain nuclei to alter neural activity. There is class I evidence for the safety and efficacy of DBS applied to the internal globus pallidus (GPi) to suppress motor symptoms in dystonia [4, 5] with an average improvement of dystonia severity of 50 to 60% in most clinical studies [5– 8]. However, there is a large variability in clinical outcome with up to 25% non-responders (< 25% motor score improvement) even in highly selected primary dystonia patients. In a large cohort of patients collected from several European centers we recently demonstrated that the variable clinical outcomes of pallidal DBS for dystonia may result to a relevant degree by the exact location and stimulation volume within the pallidal region [9].

These results and the underlying cohort of > 80 patients were subsequently used to derive probabilistic maps of anti-dystonic effects by aggregating individual electrode locations and volumes of tissue activated (VTA). These maps and novel computer algorithms showed robustness between the predicted and observed clinical improvement with an R^2^ of 0.53 (*p* < 0.01) in a leave-one-out-cross-validation. On average, individual predictions differed from observed improvements in dystonia by only 16.9 ± 11.6%. Interestingly, the computer algorithms predicted a potential improvement for the cohort and a reduction in non-responders if patients were switched to the optimal stimulation settings determined by the algorithms (mean improvement: 16.9 ± 11.6% and 25% to < 5% non-responders) [9].

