We subsequently modified the algorithms to test all possible stimulation settings of de novo patients in silico based on the expected clinical outcome and thus potentially predict the best possible stimulation parameters for the individual patients. Within the framework of a BMBF-funded study, this concept of a computer-based prediction of optimal stimulation parameters for patients with dystonia will be tested in a randomized, controlled crossover study.

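### As written, eligibility does not exclude patients whose data built the prediction maps, so the success rate could include in-sample predictions; overlap is not shown and the size of any bias is unknown

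*Protocol article*

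**What the plan says.** On the origin of the model, the Introduction of the protocol article refers to patients from several centres: "In a large cohort of patients collected from several European centers we recently demonstrated". It continues: "These results and the underlying cohort of > 80 patients were subsequently used to derive probabilistic maps of anti-dystonic effects". The abstract describes the same step as "aggregating individual electrode locations and volumes of tissue activated of > 80 patients collected in a multicentre effort". Predictions were checked "in a leave-one-out-cross-validation". On intended use, the Introduction says: "We subsequently modified the algorithms to test all possible stimulation settings of de novo patients in silico". It then states that this concept is what the trial will test.

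On who may enter, the eligibility section requires isolated dystonia treated by bilateral pallidal stimulation, more than 6 months since surgery, settings and medication stable for at least 3 months, and consent. The only exclusion is relevant "comorbidities that might interfere with study endpoints (esp. palliative disease and severe neurologic or psychiatric comorbidities".

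On analysis, the Statistical analysis section computes the exact two-sided 95% confidence interval for the success rate from all patients whose primary endpoint is defined. The sample size section uses that rate to choose between planning a superiority trial, planning an equivalence trial (or studying a combined approach), and doing further exploratory work.

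**The concern.** The trial recruits patients who already have pallidal electrodes and established settings. The maps came from patients with dystonia and pallidal stimulation, in work the authors report as their own. A member of the map cohort could meet every inclusion criterion, and the exclusion list would not stop that patient.

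For such a patient, the map that selects the computer program already holds the patient's own electrode position, stimulated volume and response. The map can then lean towards regions known to have helped that individual, or away from regions known not to have helped. A new patient has no such advantage. The group's own validation kept each case out of its own prediction; the eligibility and analysis text of the prospective trial has no matching safeguard.

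At stake is the meaning of the success rate. It is read as performance in new patients and it sets the hypothesis of the next, larger trial. If part of it is in-sample, it may be too favourable for that purpose.

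**Working it through.** **Step 1: is a contributor eligible as written?**
- The inclusion criteria concern diagnosis, target, time since surgery, stability and consent. None requires that the patient be new to the model.
- The only exclusion is comorbidity.
- The section on image-based prediction describes how settings are generated and filtered. It does not remove a patient's own data from the map.
- The analysis set is everyone with a defined endpoint, and no analysis without contributors is described.

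A contributor who meets the inclusion criteria is therefore eligible and counted.

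**Step 2: reproduce the plan's figures.** Inputs from the sample size and Statistical analysis sections: n = 40, exact two-sided 95% interval, cut-offs 27 or more / 14 to 26 / 13 or fewer. Clopper–Pearson limits for x successes are the 2.5% quantile of Beta(x, n − x + 1) and the 97.5% quantile of Beta(x + 1, n − x).

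| Successes of 40 | Exact 95% CI | Consequence |
|---|---|---|
| 27 | 50.9% to 81.4% | excludes 50% and 20% |
| 26 | 48.3% to 79.4% | excludes 80% |
| 14 | 20.6% to 51.7% | excludes 20% |
| 13 | 18.6% to 49.1% | excludes 50% |

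No count from 0 to 40 leaves two of the three rates 20%, 50% and 80% inside the interval. The stated figures reproduce. They treat the 40 patients as sharing one success rate.

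**Step 3: what overlap could do.** The documents give neither the number m of contributors among the 40 nor their success rate, so both are assumptions and are varied. Success in new patients is set at 50%, the article's middle scenario. The number of successes is

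X = Binomial(m, p_c) + Binomial(40 − m, 0.50),

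where p_c is the assumed rate in contributors. The expected rate is [m × p_c + (40 − m) × 0.50] / 40. For m = 10 and p_c = 0.80 this is (8 + 15) / 40 = 57.5%. P(X ≥ 27) comes from the exact convolution of the two binomials.

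| Contributors' success p_c | m = 0 | m = 4 | m = 10 | m = 20 |
|---|---|---|---|---|
| 55% | 1.9% | 2.2% | 2.8% | 4.0% |
| 60% | 1.9% | 2.6% | 3.9% | 7.4% |
| 70% | 1.9% | 3.4% | 7.2% | 20.6% |
| 80% | 1.9% | 4.3% | 12.2% | 43.6% |

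Entries are P(X ≥ 27). With p_c = 60% the expected rate moves from 50% to 51%, 52.5% or 55% for m = 4, 10 or 20; with p_c = 80% it moves to 53%, 57.5% or 65%. The effect is small if either the overlap or the gap in success is small. It is large only if both are large.

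**The case against.** A reader might infer that the trial does test the algorithm on its own training cases, or that its success rate is inflated. The documents support neither. They do not list the contributing centres, do not say whether the trial centre was among them, and do not say whether any cohort member is available for recruitment. The wording about de novo patients suggests that overlap was not intended, but it describes the algorithm's use and is not an entry rule.

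The article is condensed, and its eligibility list looks abridged. It does not ask for the preoperative MRI and postoperative CT that the algorithm needs, nor for the pre-operative score that the endpoint needs. The full protocol may therefore contain the exclusion. That limits how firmly the gap can be asserted, but the list as published still admits contributors.

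The mechanism is also limited. One patient among more than 80 may carry little weight in the maps, although the local weight could be larger. Leave-one-out validation protects a measure of prediction accuracy. The trial's endpoint instead compares newly obtained blinded ratings under two programs. In-sample fit cannot raise those ratings mechanically; it helps only if the patient's own past response changes which setting is selected. Upward bias is plausible, not established.

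No figure in the article supports a 30-point gap between contributors and new patients: 80% and 50% are planning scenarios, not estimates for these groups. Finally, the study is exploratory, so an optimistic rate would mislead planning and would not support a confirmatory claim.

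All of this bears on size and likelihood. None of it closes the gap in the entry rule.

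**Conclusion.** The concern holds in a limited form. The published criteria admit patients whose data built the maps, the primary analysis would count them, and nothing in the article removes their data before prediction. The success rate could therefore mix in-sample and new-patient results, although the concept under test is prediction for new patients.

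Whether this happens, and by how much it would matter, cannot be determined from the article. The range in the working, from almost no change to a chance of 43.6% of reaching 27 successes, rests wholly on assumed overlap and assumed success rates. The upper end needs half the sample to be contributors and a 30-point advantage at once. The sample size of 40 and the three cut-offs are correct and are not in question. The point merits a change because the change is cheap and the rate decides what kind of trial follows.

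**What to change.** 1. Add an exclusion criterion for patients whose imaging or outcome data contributed to the probabilistic maps. If the full protocol already has one, state it with the published criteria.
2. If contributors are already enrolled and not yet programmed, derive their computer program from maps rebuilt without their own data.
3. Report how many analysed patients contributed to the maps, and give the success rate with its exact 95% interval both with and without them.

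The target of 40 evaluable patients and the cut-offs stay as they are. The cost is one line of eligibility text, a somewhat smaller recruitment pool at contributing centres and, for any contributor already enrolled, one rebuild of the map. If contributors are dropped from an analysis, its interval is wider and the 40-patient cut-offs do not apply to it directly.

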### Perspective

DIPS is the first randomized, double-blind and controlled comparison for computer-assisted DBS programming for patients with dystonia. The purpose of this study protocol is to answer the question of which programming method is more effective in controlling the symptoms of dystonia. If superiority or equality of computer-based prediction of optimal stimulation parameters can be shown, this would have significant consequences for dystonia patients worldwide, as their programming is currently still predominantly dependent on the experience of the DBS programmer. In silico objective testing of all possible stimulation parameters within seconds would save patients lengthy programming sessions and sometimes months of programming titration.

## Data Availability

The datasets used and/or analysed during the current study will be available from the corresponding author on reasonable request.

## Abbreviations

BFMDRS: Burke–Fahn–Marsden Dystonia rating scale
CDQ24: Craniocervical dystonia questionnaire 24
DBS: Deep brain stimulation
DIPS: Dystonia Image-based Programming of Stimulation
SF-36: Short form-36
TWSTRS: Toronto Western Spasmodic Torticollis Rating Scale
VTA: Volumes of tissue activated
